#### Safety outcomes.

Patients undergo pre- and post-treatment examinations, including blood routine, urine routine, stool routine, liver and kidney function tests (ALT, AST, BUN, Cr, SUA), and electrocardiography, to assess the safety of the interventions in this study. The blood, urine, and stool specimens collected from the patients after completion of the tests are to be disposed of by medical staff according to regulations.

We employ the Common Terminology Criteria for Adverse Events (CTCAE) version 5.0 from the National Cancer Institute of the United States to document the severity of adverse events, categorized from grades 1–5 [25]. According to the classification system devised by the Drug Adverse Reaction Monitoring Center of the Chinese Ministry of Health, adverse events are classified into five levels: “definitely related, probably related, possibly related, probably unrelated, definitely unrelated.” The first three levels are deemed to be associated with the investigational medication [26]. Any adverse events during treatment will be documented based on severity and their causal assessment outcomes. In the event of serious adverse events during the study, immediate measures must be taken and reported to the research design unit’s project manager and ethics committee, which will determine whether to proceed or terminate the study. All adverse events should be monitored until appropriately resolved or stabilized.

### Data management, monitoring and auditing

Data for this trial will be collected from Case Report Forms (CRFs) at each center, with study monitors reviewing the forms to ensure completeness and quality. Two independent data managers will be responsible for entering the data into the system. Researchers will strictly maintain participant confidentiality, with access granted only by permission from the research design unit. The data management system is provided by Jiangsu Famous Medicine Co., Ltd.

The Data Monitoring Committee (DMC), organized and led by Zhejiang Chinese Medical University, comprises experienced clinical researchers and esteemed academic scholars in the field. The committee will conduct regular audits of the data to ensure the integrity and safety of the study. These audits will adhere to internationally recognized standards for clinical trial inspections, including the examination of clinical trial items, quality, and risk management, to ensure the authenticity and integrity of the research data. Once recruitment reaches 50%, the committee will perform interim analyses of the primary outcomes using Lan-DeMets with O’Brien-Fleming methodology to evaluate the study’s effectiveness and safety.

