### Sample size

The sample size calculation was performed using PASS (version 2021) with the “Comparison of two independent sample rates” calculation module. A power of 80% and an alpha level of 0.025 for a one-sided test and a superiority test were used. Based on a previous study by our team [22], the flare rates of acute gouty arthritis after 12 weeks of placebo treatment were 63.2%, and for the group treated with the QTF was 38.5%. Calculations yielded sample sizes of N1 = N2 = 61 for both the intervention and control groups, considering a dropout rate of 20%. In total, 144 patients with intermittent gout will be included, with 72 patients in both the intervention and control groups.

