### Outcomes

#### Primary outcomes.

The frequency of gout flares will be recorded at weeks 6, 12, 24, and 48.

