### Statistical analysis

The statistical analysis for this trial will be conducted based on the Per-Protocol (PP) and Intent-to-Treat (ITT) data, conducted by Jiangsu Famous Medicine Co., Ltd., situated in Nanjing, China. Different analysis methods will be employed depending on the type of data measurement or counting.

For the primary outcome, the number of gout flares in each group will be compared using t-tests or Wilcoxon rank-sum tests, with center effects controlled through covariance analysis. For count data, such as time span to the first occurrence of gout flares, duration of acute gouty arthritis recurrence, pain visual analog scale score, HAQ-DI, and safety analysis indicators (like routine blood tests), the same methods will be applied. Measurement data, including the recurrence rate of acute gouty arthritis and the incidence of adverse events, will be analyzed using chi-square tests or Fisher’s exact tests, with center effects controlled through binary or multinomial logistic regression analysis. All hypothesis tests in this study will be two-sided, with a significance level of 0.05. Differences will be considered statistically significant when p < 0.05. SAS version 9.4 will be used for all statistical analyses.

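### The primary outcome names four time points and no deciding one, the flat 0.05 rule conflicts with the planned alpha spending, and an interim tied to recruitment may have little week-12 data

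*Protocol article*

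**What the plan says.** All places are in the Methods of the protocol article.

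- **Primary outcomes:** "The frequency of gout flares will be recorded at weeks 6, 12, 24, and 48". This sentence is the whole definition.
- **Statistical analysis:** "the number of gout flares in each group will be compared using t-tests or Wilcoxon rank-sum tests". No week is given, nor whether counts are cumulative or per interval. The section adds "All hypothesis tests in this study will be two-sided, with a significance level of 0.05" and "Differences will be considered statistically significant when p < 0.05".
- **Data management, monitoring and auditing:** "Once recruitment reaches 50%, the committee will perform interim analyses of the primary outcomes using Lan-DeMets with O’Brien-Fleming methodology". The stated purpose covers effectiveness as well as safety.
- **Sample size:** "A power of 80% and an alpha level of 0.025 for a one-sided test and a superiority test were used". The planning rates are 63.2% (placebo) and 38.5% (QTF), and the placebo rate is given as a 12-week figure. There is no mention of an interim look.

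**The concern.** Three statements do not fit together.

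1. A primary endpoint needs one deciding time point, or a rule for several. Here there are four visits, no rule, and a sample size built on one of them. A reader of the final report could not tell whether success at week 6 or week 48 alone would count.
2. Alpha spending uses up part of the 5% at the interim, so the final primary test must be slightly stricter than 0.05. The analysis section applies 0.05 to every test.
3. A spending function runs on information, meaning patients with outcome data. The look is set by recruitment instead. When half the patients have been recruited, many of them cannot yet have week-12 data.

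The first point affects what may be claimed as primary success. The second is a direct contradiction with a small numerical effect. The third concerns whether the look is of any use.

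**Working it through.** **The plan's own figure.** Two proportions, unpooled variance, one-sided 0.025, power 80%:

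n = (1.960 + 0.842)² × (0.632×0.368 + 0.385×0.615) / (0.632 − 0.385)² = 7.849 × 0.4694 / 0.0610 = 60.4, so 61 per arm.

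The stated 61 is reproduced. It spends the full one-sided 0.025 on one comparison of 12-week rates.

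**Four time points, each at two-sided 0.05, success on any one.**

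- Four independent tests: 1 − 0.95⁴ = 18.5%. This is the reference for separate intervals.
- Cumulative counts at a constant flare rate: the test statistics at weeks tᵢ < tⱼ have correlation √(tᵢ/tⱼ). A multivariate normal with t = 6, 12, 24, 48 gives 14.2%.
- Null simulation with t-tests, 58 per arm. Assumptions: either one flare per 12 weeks throughout, or weekly rates falling from 1/10 to 1/40; Poisson counts, or counts over-dispersed by a gamma factor with variance up to 2.

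| Counting rule | Chance of at least one p < 0.05 |
|---|---|
| Cumulative to each visit | 9.0% to 14.2% |
| Per interval | 13.9% to 18.4% |

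**Interim look, one endpoint.** O'Brien-Fleming-type spending with one-sided α = 0.025 is α(t) = 2[1 − Φ(2.2414/√t)].

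- At t = 0.5: α = 2[1 − Φ(3.170)] = 0.001525 one-sided, so two-sided p = 0.00305 and z = 2.963.
- With correlation √0.5 between the two looks, the final boundary that keeps 5% overall is z = 1.9686, p = 0.0490.
- Leaving the final test at 1.960 gives 5.10% overall. At t = 0.4 it gives 5.03%, and at lower fractions less.

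**Information at 50% recruitment.** The article gives no accrual period, so this is a range. With uniform accrual over A weeks, the share of the 144 with 12 weeks of follow-up is (A/2 − 12)/A. Dropout is ignored.

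| Assumed accrual | Share with week-12 data | Patients |
|---|---|---|
| 26 weeks | 1/26 = 3.8% | about 6 |
| 52 weeks | 14/52 = 26.9% | about 39 |
| 104 weeks | 40/104 = 38.5% | about 55 |

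For week-48 data the same formula, with 48 in place of 12, gives none, none and 3.8%.

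**Chance of crossing the interim boundary under the planned effect.** The expected z at full information is 1.960 + 0.842 = 2.802, and at fraction t it is 2.802√t.

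- t = 0.27: boundary z = 4.16 (p = 0.00003); expected z = 1.456; power = 1 − Φ(2.70) = 0.3%.
- t = 0.50: boundary z = 2.963 (p = 0.0031); expected z = 1.981; power = 1 − Φ(0.98) = 16%.

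**The case against.** **The visits are only a recording schedule, and week 12 is implied.** The secondary outcomes use the same wording about recording, treatment lasts 12 weeks, the sample size uses a 12-week rate, and the Introduction ties post-treatment follow-up to long-term effects. This is a fair reading and the most likely intention. It stands to this extent: the 9–18.5% is conditional on a success-on-any-visit rule that the plan does not state, so it is not a property of the plan as written. It does not remove the point, because no sentence names week 12 as primary.

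**The 0.05 may be the overall level, with boundaries kept in an analysis plan or committee charter.** Numerical boundaries can indeed sit elsewhere, and their absence is not criticised here. But the article states a rule for all tests, and that rule is incompatible with the spending method for the final primary test. A reader might also infer that the interim itself is tested at 0.05, which would take one endpoint to 8.3% at half information. The documents do not support this, since the monitoring section gives the look its own method.

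**The recruitment trigger inflates the error rate.** A reader might infer this, but it does not follow. Lan-DeMets sets the boundary from the information actually observed, whenever the look occurs. What remains is low power at the look, and how low depends on an accrual period the article does not give. The look also serves safety, for which early data have value.

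**The study is called exploratory.** The Discussion does say so. The plan nevertheless uses a powered superiority comparison with a formal significance rule, so the primary claim still needs a defined endpoint and level.

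**Conclusion.** The concern holds in this form. As written, the plan does not guarantee 5% for its primary claim, and the reason is almost entirely the missing deciding time point. If any visit may count, the error is about 9–14% (cumulative) or 14–18.5% (per interval), depending on the assumed flare rates and over-dispersion. If week 12 alone was meant, that excess disappears.

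The flat 0.05 is a real contradiction with the spending method but costs only about 0.1 percentage point at half information, and less at earlier looks. The recruitment trigger costs no error control. Its fault is that the efficacy look may have almost no chance of showing anything: about 0.3% power at 27% information against about 16% at 50%, under assumed uniform accrual and the planned effect.

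**What to change.** 1. **Primary outcomes:** name flares from randomization to week 12 as the single primary time point, and make weeks 6, 24 and 48 secondary. This matches the treatment period and the sample size.
2. **Statistical analysis:** for the primary endpoint, replace the flat rule by an overall two-sided level of 0.05, with boundaries from the O'Brien-Fleming-type spending function at the observed information. At exactly 50% these are 0.0031 at the interim and 0.0490 at the final analysis.
3. **Interim trigger:** hold the look when 72 randomized patients have reached week 12 or left the study.

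The cost is a few sentences. The look comes up to about 12 weeks after the 72nd randomization, plus data cleaning. The final threshold is slightly stricter: at 61 per arm, power by the pooled formula moves from 78.6% to 78.4%.

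Keeping all four visits as alternative routes to success would cost far more. Bonferroni gives 0.0125 each, the pooled formula rises from 64 to 90 per arm, and power at 61 per arm falls to 59%.

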### Statistical analysis

The statistical analysis for this trial will be conducted based on the Per-Protocol (PP) and Intent-to-Treat (ITT) data, conducted by Jiangsu Famous Medicine Co., Ltd., situated in Nanjing, China. Different analysis methods will be employed depending on the type of data measurement or counting.

For the primary outcome, the number of gout flares in each group will be compared using t-tests or Wilcoxon rank-sum tests, with center effects controlled through covariance analysis. For count data, such as time span to the first occurrence of gout flares, duration of acute gouty arthritis recurrence, pain visual analog scale score, HAQ-DI, and safety analysis indicators (like routine blood tests), the same methods will be applied. Measurement data, including the recurrence rate of acute gouty arthritis and the incidence of adverse events, will be analyzed using chi-square tests or Fisher’s exact tests, with center effects controlled through binary or multinomial logistic regression analysis. All hypothesis tests in this study will be two-sided, with a significance level of 0.05. Differences will be considered statistically significant when p < 0.05. SAS version 9.4 will be used for all statistical analyses.

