**Method:**

This is a multi-center, randomized, double-blind, placebo, parallel-controlled clinical trial conducted in four hospitals in Zhejiang Province, China. A total of 144 patients, aged 18–80 years, will be randomly allocated to either the intervention group (QTF + febuxostat) or the control group (placebo + febuxostat) for a 12-week treatment period. The primary outcome measure is the frequency of gout flares. Secondary outcome measures include the time from the patient’s enrollment to the first occurrence of gout flare (in days), duration of gout flare (in days), health assessment questionnaire disability index (HAQ-DI), pain level (visual analog scale – VAS), rate of achieving target uric acid levels. Occurrences of adverse events, and results from electrocardiograms and laboratory tests, will be monitored.

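### The 80% power is calculated for the 12-week proportion of patients with a flare, but the primary test compares the number of flares, so its power is not known

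*Protocol article*

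**What the plan says.** The abstract of the protocol article states: "The primary outcome measure is the frequency of gout flares". The Primary outcomes section has this recorded at weeks 6, 12, 24 and 48.

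The Sample size section uses a module for "Comparison of two independent sample rates", with these settings: "A power of 80% and an alpha level of 0.025 for a one-sided test and a superiority test were used". Its inputs are the shares of patients flaring after 12 weeks in the team's previous study, 63.2% on placebo and 38.5% on the formula (QTF). The result is 61 per arm. After an allowance for 20% dropout, "144 patients with intermittent gout will be included, with 72 patients in both the intervention and control groups".

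The Statistical analysis section says of the primary outcome that "the number of gout flares in each group will be compared using t-tests or Wilcoxon rank-sum tests, with center effects controlled through covariance analysis". The recurrence rate of acute gouty arthritis appears later in the same paragraph, with adverse events, under chi-square or Fisher's exact tests. It is not called primary. The only adjustment named for the primary comparison is for centre.

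**The concern.** A power statement belongs to one endpoint and one test. Here the calculation treats each patient as flaring or not, while the primary test uses how many flares each patient had. The two agree only under particular assumptions about flares per patient, and the protocol states none. A t-test depends on the mean and variance of the counts, a Wilcoxon test on their ordering, and neither follows from the two proportions alone. The justification for 144 patients is therefore not tied to the analysis that decides the trial.

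The second issue is time observed. Flare counts accumulate over follow-up, 20% dropout is expected, and the Exit criteria section provides for withdrawal by the investigator, withdrawal at the patient's request, and loss to follow-up. Neither named test has an exposure term. If early leavers enter with the count reached so far, the arm that loses more patients will tend to show fewer flares for that reason alone.

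**Working it through.** **1. Reproducing 61 per arm** (inputs from the Sample size section)

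Two-proportion formula with unpooled variance: n = [p1(1−p1) + p2(1−p2)] × (z0.975 + z0.80)² / (p1−p2)²

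- p1(1−p1) = 0.632 × 0.368 = 0.2326
- p2(1−p2) = 0.385 × 0.615 = 0.2368
- (1.960 + 0.842)² = 7.849
- (0.632 − 0.385)² = 0.0610
- n = 0.4694 × 7.849 / 0.0610 = 60.4, so 61

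This matches the plan and confirms that the sizing is for a yes/no endpoint. One-sided 0.025 in the design and two-sided 0.05 in the analysis are equivalent for power here, so sidedness does not explain the mismatch.

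**2. Power of the named tests with the same two proportions**

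The protocol gives no count distribution, so the following are assumptions. I used 61 per arm, two-sided 0.05 and 10,000 simulated trials per row.

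*(a) QTF changes only whether a patient flares.* A patient flares with probability 0.632 or 0.385. A patient who flares has 1 flare plus a number of extra flares with the same distribution in both arms.

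| Mean flares per flaring patient | Dispersion of the extra flares | t-test | Wilcoxon |
|---|---|---|---|
| 1.3 | 0 (Poisson) | 66% | 74% |
| 2 | 0 | 61% | 72% |
| 2 | 1 | 51% | 73% |
| 3 | 1 | 45% | 72% |
| 2 | 2 | 44% | 73% |
| 3 | 2 | 36% | 72% |

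Other assumed spreads gave about 43–66% (t-test) and 70–76% (Wilcoxon), and I carry those ranges forward. The last row shows that the t-test can fall lower if a few patients flare very often.

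*(b) QTF lowers the flare rate.* Counts are Poisson or negative binomial with dispersion k, and the means are set so that the share without a flare is 0.368 and 0.615: mean = −ln(P0) if k = 0, otherwise (P0^−k − 1)/k.

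| k | Mean, placebo | Mean, QTF | Rate ratio | t-test | Wilcoxon |
|---|---|---|---|---|---|
| 0 | 1.00 | 0.49 | 0.49 | 91% | 89% |
| 0.5 | 1.30 | 0.55 | 0.42 | 95% | 90% |
| 1 | 1.72 | 0.63 | 0.36 | 97% | 93% |

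Both sets have the same 63.2% and 38.5%, and a chi-square test on the proportions has about 80% power in either.

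**3. Time observed**

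Assumptions: no treatment effect, 72 per arm, mean of 1 flare over 12 weeks, leavers exit at a uniform time, raw counts analysed, dispersion 0 to 2.

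| Dropout by arm | t-test type I error | Wilcoxon type I error |
|---|---|---|
| 20% v 20% | 4.8–5.0% | 4.8–5.4% |
| 15% v 25% | 5.0–5.9% | 5.5–6.0% |
| 10% v 30% | 6.6–9.6% | 6.9–9.8% |

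In the last row mean exposure is 1 − 0.10/2 = 0.95 v 1 − 0.30/2 = 0.85. The ratio is 0.895, so raw mean counts differ by about 11% with no drug effect.

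**The case against.** The strongest reply is that the mismatch may do no harm. A formula that prevents flares would plausibly lower the rate in every patient, and the count tests then have more than 80% power. The low t-test figures need two things together: flares per flaring patient unchanged by treatment, and a t-test kept for skewed counts although Wilcoxon is the stated alternative. With Wilcoxon the shortfall is at most about 10 points. This stands. A reader might infer that the trial is underpowered; the documents do not support that, because the direction depends on a distribution they do not give. What remains is that 80% was not derived for the named test.

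On time observed, the protocol never says that early leavers enter with raw counts, and rules for incomplete follow-up often sit in a fuller plan. It predicts no difference in dropout between arms. A reader might infer that the expected 20% dropout biases the comparison; with equal dropout it does not inflate the type I error. What stands is that the primary test is already named and has no exposure term.

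Two further inferences should be resisted. A rank comparison can be adjusted for centre, by rank-based analysis of covariance or the van Elteren test, so naming Wilcoxon beside a centre adjustment is not an error in itself. And leaving out prior-year flares as a covariate is not a mistake: the Inclusion criteria require at least two, but nothing in the document says how well that count predicts later flares.

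Finally, the Discussion calls the study exploratory. That softens the consequence, but the protocol still claims 80% power and names a deciding test.

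**Conclusion.** The point holds as a stated mismatch within the protocol. The powered endpoint is the 12-week proportion with a flare; the tested endpoint is the number of flares. Reading frequency as proportion does not rescue the calculation, because the Statistical analysis section handles the two separately and ties only the count to the primary outcome.

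At 61 per arm, power of the primary test is about 43–66% (t-test) or 70–76% (Wilcoxon) in one assumed setting and about 89–97% in the other. The direction of the error is unknown.

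The missing exposure term is a secondary weakness. It matters only if dropout is clearly unequal: type I error is about 7–10% at an assumed 10% v 30%, under 6.5% at 15% v 25%, and about 5% when equal.

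**What to change.** Choose one primary endpoint at one time point, with one test and a power statement for that test.

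- **(a) Keep the count.** Define it as flares from randomization to week 12. Analyse it by negative binomial regression with log(time observed) as offset and centre as covariate, and report a rate ratio with 95% CI. State that the 80% refers to the proportion, or restate power for the count under a stated mean and dispersion.
- **(b) Make the proportion primary.** Use the share with at least one flare by week 12, analysed by logistic regression with centre. This matches the calculation already done. It does not remove sensitivity to unequal dropout, so a rule for patients who leave before week 12 is still needed.

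Adjusting for prior-year flares is an optional improvement if the exact number is recorded; eligibility needs only that it be at least two.

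The cost is rewording the Sample size and Statistical analysis paragraphs. Option (a) has a downside: the offset assumes a constant flare rate and exit unrelated to flares. Exit for medication outside the protocol could follow a flare, so a sensitivity analysis is needed. The change should be made before the interim analysis at 50% recruitment, which uses the same primary outcome.

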**Fig 1 pone.0327864.g001:**
[figure not shown]
Study procedure. ^a^Observe continuously throughout the study and record when it occurs. ^b^Including the number of acute flares of gouty arthritis, the time span from randomization to the first occurrence of an acute attack, and the duration of recurrent acute gouty arthritis. ^c^Red blood cell count (RBC), white blood cell count (WBC), hemoglobin (HGB), neutrophil percentage (NEU), platelet count (PLT). ^d^Alanine aminotransferase (ALT), aspartate aminotransferase (AST). ^e^Blood urea nitrogen (BUN), creatinine (Cr), serum uric acid (SUA).Qu-zhuo Tong-bi formula(QTF).

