#### Secondary outcomes.

1. The Time span from patient’s enrollment to the first occurrence of gout flares (in days); 2. Duration of gout flares (in days); 3. Health Assessment Questionnaire Disability Index (HAQ-DI) for quality-of-life assessment; 4. Changes in visual analog scale (VAS). 5. Rate of achieving target uric acid levels (Compliance rate = number of eligible patients/total number of patients under observation x 100%; Standard: Gout treatment achievement is defined as lowering serum uric acid levels to below 360 umol/L through the use of uric acid-lowering medications). Outcomes 1–4 will be recorded at weeks 6, 12, 24, and 48. Outcome 5 will be recorded at weeks 12, 24, and 48.

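### Time to first flare is to be tested by t-test or Wilcoxon with no provision for censoring, although about half the patients are expected to be flare-free at week 12; flare duration needs a separate remedy

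*Protocol article*

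**What the plan says.** The Statistical analysis section first gives the method for the primary outcome: flare counts are "compared using t-tests or Wilcoxon rank-sum tests, with center effects controlled through covariance analysis". It then continues: "For count data, such as time span to the first occurrence of gout flares, duration of acute gouty arthritis recurrence", together with pain, HAQ-DI and laboratory values, and for all of these "the same methods will be applied". So the article names a method for both flare-timing outcomes. It mentions no survival method, no censoring rule, and no value for a patient who never flares.

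Under Secondary outcomes, the first item is "The Time span from patient’s enrollment to the first occurrence of gout flares (in days") and the second is "Duration of gout flares (in days"). The schedule is "Outcomes 1–4 will be recorded at weeks 6, 12, 24, and 48". The Abstract also counts from enrolment, but the Fig 1 legend describes "the time span from randomization to the first occurrence of an acute attack".

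The Sample size section states that "the flare rates of acute gouty arthritis after 12 weeks of placebo treatment were 63.2" percent, with 38.5% on QTF, and allows for 20% dropout. The end of the Introduction makes a longer time to flare and a shorter flare duration explicit aims.

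**The concern.** A t-test or Wilcoxon test needs one number per patient. A patient who has not flared by the end of follow-up, or who leaves before flaring, has no observed time to first flare; it is known only to exceed the time observed. The analyst must leave such patients out or assign them a value, and the article does not say which.

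Leaving them out selects on an event after randomization that the treatment is meant to prevent. Assigning the last follow-up day treats a dropout as if a flare had occurred that day. The choice affects about half the trial, unevenly between arms, and could be made after the data are seen. At stake is the answer to a stated study aim.

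Flare duration raises a different problem. In a patient with no flare it is undefined, or zero, but not censored. A between-arm test among those who flare compares subsets that randomization did not form.

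**Working it through.** **Inputs.** From Sample size: 12-week flare rates p1 = 0.632 (placebo) and p2 = 0.385 (QTF), one-sided alpha 0.025, power 80%, 61 per arm before and 72 per arm after the dropout allowance, dropout 20%. From Statistical analysis: two-sided tests at 0.05. Assumption: constant hazards within each arm.

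**1. The plan's own figure.** Unpooled two-proportion formula:
n = (1.960 + 0.842)² × [0.632×0.368 + 0.385×0.615] / (0.632 − 0.385)² = 60.4, rounded up to 61. This matches the stated 61 per arm, so the rates are read as the plan uses them.

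**2. Flare-free patients at week 12.** Placebo 1 − 0.632 = 36.8%; QTF 1 − 0.385 = 61.5%. With 72 per arm: 72 × 0.368 = 26.5 and 72 × 0.615 = 44.3, together 70.8 of 144, or 49%.

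**3. Implied hazards.** λ = −ln(1 − p)/84 per day. The ratio is ln(0.615)/ln(0.368) = 0.486. The model medians, ln 2/λ, are 58 days (placebo) and 120 days (QTF).

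**4. Flarers only.** The mean time among those who flare by day 84 is 1/λ − 84(1 − p)/p.
- Placebo: 84.0 − 84×0.368/0.632 = 35.1 days.
- QTF: 172.8 − 84×0.615/0.385 = 38.6 days.

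The gap is 3.5 days, although the medians differ by about 62 days.

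**5. Log-rank benchmark at 72 per arm.** Expected first flares: 72 × (0.632 + 0.385) = 73.2. Schoenfeld: √73.2 × |ln 0.486| / 2 − 1.96 = 1.12, so power is about 87%. Simulation without dropout gives 88%.

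**6. Simulated rejection rates by handling** (two-sided 0.05, constant hazards):

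| Situation | t-test | Wilcoxon | Log-rank |
|---|---|---|---|
| Flarers only, to week 12 (61 or 72 per arm) | about 8–10% | about 8–10% | 80–88% |
| Flare-free set to day 84, full follow-up, 61 per arm | about 73% | about 79% | 80% |
| Last follow-up day, 20% dropout in each arm, 72 per arm | about 66% | about 70% | 83% |
| No effect, assumed dropout 10% v 30%, last follow-up day, 72 per arm | about 14–21% (both tests) | as left | about 5% |
| Flarers only, hazard extrapolated to week 48, 72 per arm | about 80% | about 75% | 98–99% |

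The fourth row is type I error; the others are power. Its range covers variants of the simulation. With both arms at the placebo hazard it is 16% (t) and 17% (Wilcoxon). With no effect and complete follow-up, or equal 20% dropout, last-follow-up-day handling keeps type I error near 5%.

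**7. Week 48.** Extrapolating the hazards over 336 days, 0.368⁴ = 2% of placebo and 0.615⁴ = 14% of QTF patients stay flare-free. The problem shrinks but does not vanish.

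**8. Flare duration.** The documents give no expected durations, so no size is computed. On the plan's rates, a week-12 comparison would set about 46 placebo patients (72 × 0.632) against about 28 QTF patients (72 × 0.385).

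**The case against.** A reader might infer that the planned test has almost no power, or that the comparison is simply biased. The article supports neither. The 8 to 10% belongs to a flarers-only analysis at week 12, and the article does not say that flare-free patients are left out; it names intention-to-treat as well as per-protocol analysis. Wilcoxon is one of the two named tests. With flare-free patients tied at day 84 and complete follow-up, it compares the randomized groups validly and loses almost nothing to log-rank (79% v 80% at 61 per arm). These outcomes are also recorded to week 48, where even a flarers-only test does much better if the hazard stays constant. This all stands. What remains is that follow-up is not expected to be complete, and that the handling is left open.

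It could be said that such detail belongs in an analysis plan not shown here. That would excuse silence, but the article names a method, and the method does not suit a censored outcome.

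Flare duration does not share the censoring fault, and duration among patients who flare is a legitimate clinical description. The objection holds against treating the two outcomes alike, but not against the caution on a between-arm test.

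Both outcomes are secondary, the sample size rests on flare rates, and the Discussion calls the study exploratory. This limits how serious the point is. The enrolment and randomization wordings do conflict, but nothing shows a material gap between the two dates.

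**Conclusion.** The point holds in limited form. The stated method for time to first flare cannot handle censoring, and the plan's own rates and dropout allowance make censoring common. The cost depends on an unstated choice: near-total loss of power at week 12 if only flarers are compared, and little loss if flare-free patients are ranked last and follow-up is complete. With the planned 20% dropout, last-follow-up-day handling loses about 13 to 17 percentage points of power against log-rank. Unequal dropout can also raise the false-positive rate to about three or four times the nominal level. The last result rests on an assumed 10% v 30% split that the article does not predict, and all the figures rest on constant hazards.

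For flare duration the fault is selection, not censoring, and its size is not established. This should be fixed before analysis. It does not threaten the primary comparison of flare frequency.

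**What to change.** **Time to first flare.** In Statistical analysis, take this outcome out of the t-test/Wilcoxon sentence. State Kaplan-Meier curves with a log-rank test and a Cox model, both stratified by centre, with flare-free patients censored at last contact or at the end of the analysis period, whichever is earlier. Count from randomization, and use that origin in the Abstract, Secondary outcomes and the Fig 1 legend.

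**Flare duration.** Label duration per flare as descriptive. Where onset and end dates are recorded, add total flare days per randomized patient, with 0 for none, as the between-arm comparison.

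**Cost.** The first change is wording, plus a last-contact date for each patient; days to first flare are already an outcome. The second also changes Secondary outcomes and depends on onset and end dates. The rule to contact staff within 24 hours covers flares in the treatment period, so check whether dates after week 12 are precise enough. Neither change needs more patients or visits.
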